## Method

### Study design

Details about this trial are captured in the SPIRIT (Standard Protocol Items: Recommendations for Interventional Trials) checklist [54, 55] in Appendix A of the online supplemental materials (OSM) and Fig. 1. This study is a two-arm, parallel-group RCT that aims to test the efficacy of Digital PAI relative to a Self-Monitoring Placebo control in adults with mild-to-moderately severe anxiety or depression. After providing informed consent and completing the Qualtrics-administered baseline self-report battery, participants will be randomized in a 1:1 ratio (*n* = 600 per condition) using a computer-generated random number sequence embedded in the Qualtrics platform. In other words, participants are randomized into the Digital PAI or Self-Monitoring Placebo control group at the end of the baseline assessment using the built-in randomizer function in Qualtrics. The sequence is stratified by race and sex to ensure balanced allocation across key demographic strata. Immediately after completing the baseline assessment, Qualtrics automatically assigns participants to either the 6-week, low-intensity, guidance-on-demand Digital PAI or the 6-week Self-Monitoring Placebo, both of which are accessed via the mEMA Ilumivu software. The allocation sequence is concealed from the lead principal investigator (PI) and study analyst via automated assignment coding; both remain blinded to treatment group assignments until after data collection is complete.

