### Sample size and power

The *R* package *simr* [56] was used for power calculations, which simulated a multilevel model with time and group as fixed effects. The primary outcomes are anxiety and depressive symptoms, indexed by GAD-7 and PHQ-9 scores, respectively. Given the low-intensity nature of the Digital PAI and its evaluation against a Self-Monitoring Placebo as a placebo control [57], we expected the between-treatment effect sizes to range from small (Cohen’s *d* = 0.2) [26, 58] to moderate (*d* = 0.5) [24]. To achieve a statistical power of 81% while detecting small to moderate between-group efficacy effect sizes at a 5% significance level, a sample size of between 300 and 1,600 is required. Accounting for an estimated 50% attrition rate, our planned sample size was 1,200 (600 participants per group).

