### Digital phenotyping in randomly selected subsamples

To supplement self-reported assessments, we included digital phenotyping through passive sensor wearables to objectively measure behavioral and physiological indices related to mental health. This method centers on assessing key outcomes, such as heart rate (HR) variability (HRV), step counts, and sleep-wake cycles, which have been shown to correlate with affect [100] and neurocognition [101]. During each baseline visit, participants are randomly selected to be given a consumer-grade Vivosmart^®^ passive sensor wearable (Garmin, Olathe, KS, USA) in conjunction with the “Garmin Connect” app embedded in the mEMA Ilumivu platform on their smartphones. Given budget constraints that allowed for the purchase of 25 waterproof wearables, participants from both treatment and control groups will be randomly selected. These participants will be invited to download, install, and allow the passive sensor to work together with the thrice-daily EMA surveys. These sensors will be worn continually by selected participants throughout the 6-week intervention phase, with encouragement to use them at least 70% of the time (i.e., ≥ 17 h daily, 5 days per week). This usage threshold will facilitate optimal multiple imputation of missing data from wearables [102]. These instructions were standardized by the PI and delivered by trained research personnel at the baseline visit. The wearable will capture the following dimensions of data during the 6-week intervention phase: geolocation [103], HRV-inter-beat intervals (IBIS) [104], HRV-root mean square of successive differences (RMSSD) [105], HRV-spectrum of frequencies [106], wear-time markers [107], and sleep actigraphy indicators [108, 109] (refer to Appendix B for more details). These wearable data, including geolocation, are captured to model context- and time-related patterns of everyday activity and mobility that can mediate or moderate the association between EMIs and changes in affective or clinical endpoints.

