#### Statistical approaches for primary and secondary outcomes

Prospective analyses of primary and secondary continuous outcomes, such as anxiety and depressive symptom severity (GAD-7 and PHQ-9), anhedonia (DARS), and PA (PANAS), will be analyzed using multilevel modeling (MLM) with restricted maximum likelihood estimation (REML). Piecewise MLM will be used to assess between-group differences in changes across unique timeframes (e.g., baseline to post-treatment vs. post-treatment to 3-month follow-up), enabling the estimation of distinct linear slopes before and after critical time points to model nuanced changes in clinical outcomes over time. The MLM models will consist of fixed effects of group (Digital PAI vs. Self-Monitoring Placebo) and two-way group-by-time interaction to account for within-person associations. We will use the *nlme* package [121] for all analyses, assuming random intercepts and slopes for all models. Level 1 will model within-person changes over time, and Level 2 will capture between-person factors. All outcomes will be modeled across recurring time points (baseline, mid-treatment [Week 3], post-treatment [Week 6], as well as 3-month, 6-month, and 12-month follow-ups), aligned with this RCT’s assessment schedule. Covariates will include demographic variables (e.g., age, sex), baseline symptom severity, and device wear time, where relevant, for variables that significantly differed between groups at baseline. Between- and within-group effect sizes will be computed for all outcomes of interest [119, 122]. For binary clinical outcomes, such as depression remission indexed by PHQ-9 ≤ 4, generalized estimating equations (GEE) will be utilized to estimate between-group efficacy across all time points and follow-ups, accounting for repeated assessments with an exchangeable working correlation structure [123, 124]. Standard MLM with a logistic linking function will also be conducted as a sensitivity analysis for binary outcomes [125].

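### Covariates for the primary and secondary models are chosen by a baseline significance test; they should be fixed in advance, include race and sex, and use baseline once

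*Protocol article*

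**What the plan says.** The section on statistical approaches for primary and secondary outcomes names demographic variables with two examples ("Covariates will include demographic variables (e.g., age, sex") and continues with "baseline symptom severity, and device wear time, where relevant, for variables that significantly differed between groups at baseline". The closing condition governs the list. The same section makes baseline one of the modelled outcome visits. It gives the fixed part of the model as "fixed effects of group (Digital PAI vs. Self-Monitoring Placebo) and two-way group-by-time interaction", alongside piecewise linear slopes, random intercepts and random slopes.

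Three other places bear on this:

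- Study design: "The sequence is stratified by race and sex to ensure balanced allocation across key demographic strata".
- Digital phenotyping: "These sensors will be worn continually by selected participants throughout the 6-week intervention phase", with the subsample limited by cost ("Given budget constraints that allowed for the purchase of 25 waterproof wearables").
- Sample size and power: the simulation "simulated a multilevel model with time and group as fixed effects".

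**The concern.** Random allocation makes every true baseline difference zero. A baseline test therefore finds only chance, and it selects covariates by accident and not by how well they predict outcome. The analysis model becomes a function of the data, and two analysts with different candidate lists could fit different primary models.

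The rule also works against the design. Race and sex were important enough to stratify on, and stratifying makes a significant imbalance in them unlikely. The variables most deserving of a place are thus the least likely to get one.

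Two further features of the paragraph need settling:

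- Wear time is recorded after randomisation, so it has no baseline value on which the rule could act.
- Baseline severity is offered as a covariate although baseline is already an outcome visit. The model as stated still leaves the two arms free to start at different means.

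**Working it through.** **Inputs from the article.** Effect size d = 0.2 (lower end), 600 per arm, 50% attrition, 5% significance level (two-sided assumed). This leaves 600 × 0.5 = 300 completers per arm. The article gives no correlation between visits and no variance explained by the strata, so those are assumed and shown as ranges. It states no figure for the effect of the covariate rule, so there is none to reproduce.

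**1. How often the screen admits a covariate.** For a prognostic covariate that was not a stratification factor, the test is significant by chance with probability 0.05. In 8,000 simulated trials per setting the observed rate was 4.6 to 5.2%.

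**2. What the screen does to a plain comparison at one follow-up visit.** Always adjusting multiplies the outcome SD by √(1 − ρ²), where ρ is the covariate–outcome correlation. Unadjusted power at d = 0.2 with 300 per arm is 0.688.

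| ρ (assumed) | Always adjust | Adjust only if significant | Type I error of the screened rule |
|---|---|---|---|
| 0.3 | 0.728 | 0.691 | 0.048 |
| 0.5 | 0.807 | 0.707 | 0.048 |
| 0.7 | 0.929 | 0.702 | 0.037 |

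The screen loses nearly all of the available gain, and type I error does not rise.

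**3. Leaving out balanced strata.** If the strata explain a share R² of outcome variance, the true level of an unadjusted 5% test is about 2[1 − Φ(1.96/√(1 − R²))]. For assumed R² of 2%, 5% and 10% this is 0.048, 0.044 and 0.039. The omission is conservative and costs efficiency.

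**4. Does step 2 carry over to the stated longitudinal model?** Not for group-by-time. I fitted the model with baseline as an outcome visit (complete data, visits at weeks 0, 3 and 6, group free at baseline), with and without a person-level covariate as a main effect. The group-by-time estimate was identical in each data set, whether the covariate was the baseline score or another prognostic variable. Step 2 therefore applies to comparisons at a visit. The covariate does help once the arms are constrained equal at baseline. With an illustrative covariate correlated 0.6 with the random intercept, the variance of group-by-time fell from 0.00805 to 0.00732 at an intraclass correlation (ICC) of 0.3.

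**5. What the baseline constraint is worth.** Scale time to 0, 0.5, 1, with residual variance σ², random-intercept variance τ² and random-slope variance ω². One person's fitted line has:

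- slope variance 2σ² + ω²
- intercept variance (5/6)σ² + τ²
- covariance −σ²

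Fixing the baseline difference at zero multiplies the variance of group-by-time by

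1 − 1 / [(2 + ω²/σ²)(5/6 + τ²/σ²)].

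- ICC 0.3, so τ²/σ² = 0.3/0.7 = 0.429, and ω² = 0: 1 − 1/(2 × 1.262) = 0.604.
- ICC 0.6, so τ²/σ² = 0.6/0.4 = 1.5, and ω² = 0: 1 − 1/(2 × 2.333) = 0.786.
- ICC 0.6 with ω² = 0.5σ²: 1 − 1/(2.5 × 2.333) = 0.829.

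The range is about 60 to 83%. In standard errors this is √0.604 = 0.78 to √0.829 = 0.91, a reduction of 9 to 22%.

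**6. The unlisted time term.** I simulated both arms changing by −0.3 or −0.5 SD with no treatment effect. A literal fit with group coded 0/1 and no time term gave a group-by-time coefficient of −0.30 or −0.50. With time included, or with a separate slope per arm and the two slopes contrasted, the estimate was about 0.

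**The case against.** The case against a stronger finding is good, and much of it stands.

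- **False positives from the missing time term.** A reader might infer that the plan will count improvement common to both arms as a treatment effect. The documents do not support that. The same section promises distinct slopes before and after key time points and within-person change at Level 1, and the power model has time in it. The list of fixed effects is probably incomplete, and software that expands group as a factor would fit one slope per arm. A clarification is still worthwhile, because the sentence taken literally goes wrong.
- **A large sample-size penalty from the screen.** A reader might charge the screen with the whole gap between a baseline-adjusted and a change analysis, (1 + r)/2, or 65 to 80% of the variance at an assumed r of 0.3 to 0.6. Step 4 shows otherwise: with baseline already an outcome, adding it as a covariate leaves group-by-time unchanged. That gain comes from the baseline constraint or from a post-baseline model.
- **Wear time in the primary model.** It is qualified as applying where relevant, and it exists only for participants given one of 25 devices. It was most likely meant for wearable analyses. The sentence does not say so, and its baseline condition cannot apply to wear time.
- **Race.** The demographic examples form an open list, so race is not excluded. It would still face the same screen.

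None of this rescues the rule. The article states how covariates will be selected; it does not leave the choice to a later document.

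**Conclusion.** The point holds as a should-fix. The article fixes a covariate rule that selects by chance, leaves the primary model undetermined until the data are seen, and in effect omits race and sex. The harm is data-dependence and lost precision. Type I error is not inflated and, if anything, falls slightly. The precision lost to the screen shows in comparisons at a visit and in a baseline-constrained model, not in group-by-time as now specified.

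The larger gain in precision is a separate matter. Constraining the arms equal at baseline would bring the variance of group-by-time to about 60 to 83% of its present value. That rests on an assumed ICC of 0.3 to 0.6, a linear slope over weeks 0, 3 and 6, a random-slope variance between zero and half the residual variance, and complete data.

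**What to change.** Replace the covariate sentence with:

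> Race and sex (stratification factors) are covariates in all efficacy models whatever the observed balance; no covariate is selected by a baseline test; device wear time is used only in wearable-subsample analyses and not in treatment-effect models.

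If age or another predictor is wanted, name it now on the same terms.

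Then state how baseline is used, choosing one of two forms:

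1. Keep baseline as an outcome visit, constrain the arms to a common baseline mean, and do not add baseline severity as a covariate.
2. Model post-baseline visits only, with the baseline score as a covariate.

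As a clarification, list the piecewise time main effects beside the group-by-time terms.

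The cost is wording only. The variables are already collected, recruitment is under way, and the analyst is to stay blinded until data collection ends, so the change can be made before any unblinded look at outcomes.

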### Statistical analysis plan

#### Data processing and missing data management

All preprocessing steps and data analyses will be conducted using the *R* software [113]. Using an intention-to-treat (ITT) approach, we will estimate between-group treatment efficacy for continuous and binary clinical outcomes [114]. A complier average causal effects (CACE) analysis will also be conducted to determine treatment efficacy between high- and low-potential engagers [115]. Before conducting the key data analyses, a series of preprocessing steps will be undertaken. These include anomaly diagnostics, assumption checks (e.g., linearity, multivariate normality), and random forest imputation of missing data. Random forest imputation with the *missRanger* package [116] will be used instead of multiple imputation because it better handles nonlinear associations and interactions and generates improved performance even under missing not-at-random (MNAR) conditions [117]. Sensitivity analyses will be conducted by examining outcomes under two alternative missing data management approaches, full information maximum likelihood (FIML) and multiple imputation [118]. The point estimates and 95% confidence intervals (CIs) of all effect sizes, Cohen’s *d* for continuous outcomes [119], as well as odds ratios [ORs] and risk ratios [RRs] for binary outcomes [120], will also be computed consistently.

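### The GEE and its logistic multilevel sensitivity analysis estimate different odds ratios, so their sizes cannot be compared as planned

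*Protocol article*

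**What the plan says.** All of this is in the statistical analysis plan of the protocol article.

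- **Main analysis of binary outcomes** (Statistical approaches for primary and secondary outcomes): remission, for instance a PHQ-9 score of 4 or less, is the example given. For such outcomes the plan states that "generalized estimating equations (GEE) will be utilized to estimate between-group efficacy across all time points and follow-ups". The working correlation is to be exchangeable.
- **Sensitivity analysis** (same section): "Standard MLM with a logistic linking function will also be conducted as a sensitivity analysis for binary outcomes".
- **Random effects** (same section, earlier, where the continuous-outcome models are described): "assuming random intercepts and slopes for all models".
- **Effect measures** (Data processing and missing data management): point estimates and 95% confidence intervals are promised for effect sizes, "as well as odds ratios [ORs] and risk ratios [RRs] for binary outcomes".

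The article does not say that the two models' odds ratios are different quantities, whether the MLM will be averaged over its random effects, or which feature of the two results (size, direction or test) will be compared.

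**The concern.** A sensitivity analysis should aim at the same quantity as the main analysis under different assumptions. Here the quantity itself changes. A logit-link GEE compares the odds of remission between the two arms as populations. A logistic model with random effects compares the odds for a person whose random effects are held fixed. Odds ratios are non-collapsible, so averaging the conditional model over people gives a marginal odds ratio closer to 1.

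The article commits to reporting odds ratios, so followed as written it puts two unlike figures side by side as main and sensitivity result. One reader may take the larger MLM figure as support for a bigger benefit. Another may take the gap as a sign of fragility. Neither follows. Remission matters here because the first a priori hypothesis (Study aims and hypotheses) includes it among the clinical outcomes.

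**Working it through.** **Inputs.** The article gives no remission rate, odds ratio or between-person variance for a binary outcome, so there is no figure of its own to reproduce. Assumed for illustration: remission of 30% in control and 38% in Digital PAI, a logit link, a normal random intercept with the same SD in both arms, and SD from 1 to 3.

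**Step 1: marginal odds ratio (the GEE target).**

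(0.38 / 0.62) / (0.30 / 0.70) = 0.6129 / 0.4286 = 1.43.

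**Step 2: conditional odds ratio (the MLM target).** For each SD s, find the conditional intercepts a (control) and b (Digital PAI) that satisfy

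E[expit(a + s·Z)] = 0.30 and E[expit(b + s·Z)] = 0.38, with Z standard normal.

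The expectation is taken by Gauss-Hermite integration. The conditional odds ratio is exp(b − a), and the latent-scale ICC is s² / (s² + π²/3).

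| SD | ICC | a | b | b − a | Conditional OR | Excess over 1.43 |
|---|---|---|---|---|---|---|
| 1 | 0.23 | −1.018 | −0.591 | 0.427 | 1.53 | 7% |
| 1.5 | 0.41 | −1.188 | −0.690 | 0.497 | 1.64 | 15% |
| 2 | 0.55 | −1.384 | −0.805 | 0.579 | 1.78 | 25% |
| 2.5 | 0.66 | −1.598 | −0.930 | 0.668 | 1.95 | 36% |
| 3 | 0.73 | −1.823 | −1.062 | 0.762 | 2.14 | 50% |

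Every row describes the same population, with 30% and 38% in remission. No model is misspecified and no data are missing.

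**Step 3: cross-check.** The usual approximation is log OR(conditional) ≈ log OR(marginal) × √(1 + 0.346·s²). At SD 2 this gives exp(0.3577 × √2.384) = exp(0.552) = 1.74, close to the exact 1.78.

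**Step 4: other effect sizes, control remission still 30%.**

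| Marginal OR | Conditional OR, SD 0.5 | SD 1 | SD 2 | SD 3 |
|---|---|---|---|---|
| 1.0 | 1.00 | 1.00 | 1.00 | 1.00 |
| 1.5 | 1.53 | 1.62 | 1.93 | 2.37 |
| 2.0 | 2.08 | 2.30 | 3.10 | 4.43 |

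With no effect the two agree at every SD. With an effect, the gap grows with both the effect and the SD.

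**Step 5: do the tests diverge?** For each scenario, 200 trials were simulated with 600 people, 5 visits, complete data, random-intercept SD 2 and control intercept −1.5. Each was fitted by exchangeable GEE with robust standard errors and by a random-intercept logistic model.

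| True conditional log OR | GEE OR (mean) | MLM OR (mean) | Mean z, GEE / MLM | Rejection, GEE / MLM | Same decision |
|---|---|---|---|---|---|
| 0.6 | 1.48 | 1.87 | 3.13 / 3.14 | 89% / 90% | 99% |
| 0 | 1.01 | 1.01 | 0.07 / 0.06 | 5.0% / 5.5% | 99.5% |

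The z-values correlated 0.99 in both scenarios. The odds ratios differ clearly, but direction and test result hardly differ at all.

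**Step 6: random slopes, if the logistic model has them.** Between-person variance then changes over follow-up, and so does the gap. Assume intercept SD 1.5 and an uncorrelated slope contributing SD 1.5 by the end of follow-up, so the total SD rises from 1.5 to √(1.5² + 1.5²) = 2.12. With conditional intercept −1.5 and a constant conditional odds ratio of exp(0.6) = 1.82, the marginal odds ratio is 1.55 at the start and 1.43 at the end. An effect that is constant in the MLM would look as if it were waning in the GEE. Tests were not simulated for this case.

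**The case against.** The strongest reply is that the article never says the sizes of the odds ratios will be compared. Comparing direction and inference between a GEE and a logistic MLM is legitimate, and how to average a model is detail that an article may leave to a fuller plan. The first part stands in one respect. A reader might infer that the comparison says nothing about robustness, and that is not supported: with random intercepts the two models share the null and the direction of effect, and the simulated decisions agreed in about 99% of trials. A reader might also infer that the MLM will always show a larger benefit. That is wrong too. With no effect both odds ratios are 1, a harmful effect would look more harmful, and sampling error intervenes in any single trial.

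The reply does not remove the point. The article itself chooses this pair of models, gives the second the role of sensitivity analysis and commits to reporting odds ratios, without limiting the comparison to direction and test.

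Three further objections deserve weight:

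- The wording on random intercepts and slopes sits in the description of the continuous-outcome models. Extending it to the logistic model is an interpretation. The main point needs only a random intercept.
- No link is named for the GEE. A log link, or standardisation after the GEE, could supply the promised risk ratios, so that promise is not shown to be unmet.
- A logistic MLM fitted by maximum likelihood can use incomplete repeated data, which is valuable when 50% attrition is expected (Sample size and power). That is a reason to keep the MLM, and no reason to leave its odds ratio unaveraged.

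**Conclusion.** The point holds in limited form: as planned, the sizes of the two odds ratios are not comparable. Under the assumed 30% against 38% remission, the GEE targets 1.43 and the MLM 1.53 to 2.14 for a random-intercept SD of 1 to 3. The upper end needs an ICC of 0.73, and both the rates and the SDs are assumptions, since the article supplies neither. The direction of the gap rests only on a true effect and between-person variation; its size depends on the assumed values.

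Direction and test result remain informative, at least with random intercepts only. The stakes are modest. The primary outcomes are GAD-7 and PHQ-9 severity, and neither the main GEE estimate, its test nor the sample size changes.

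**What to change.** Keep the logistic MLM as the sensitivity analysis and add two sentences to the plan:

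1. After fitting the logistic MLM, average the predicted probabilities over the estimated random-effects distribution for each arm and visit. Report the marginal risk difference, risk ratio and odds ratio with 95% confidence intervals, and compare these with the GEE.
2. Where the unaveraged MLM odds ratio is shown, label it conditional and compare only its direction and test result with the GEE.

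In the example, averaging returns 30% and 38% at every SD: a risk difference of 8 percentage points, a risk ratio of 0.38 / 0.30 = 1.27 and an odds ratio of 1.43. Any remaining gap from the GEE would then bear on the modelling assumptions and sampling error. The averaging also yields the promised "risk ratios [RRs] for binary outcomes" directly from the MLM, which a logit coefficient does not.

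The cost is a small amount of analysis code, including bootstrap or delta-method intervals. No new data are needed and the main analysis does not change.
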